### **9.3 Procedures at each visit**

#### **9.3.1 Baseline Day 0, Visit 1**

All patients presenting to the GP with a diagnosis of post-infectious cough following an URTI will be informed about the study, allowed sufficient time to ask questions and invited to participate. Patients who agree to participate are going to be screened for eligibility by taking their medical history, physical examination including vital signs, lab tests (if indicated and at the discretion of the GP). Informed consent will be obtained in writing from all participants. GPs will complete an individual CRF with participant's baseline socio-demographic information: age, sex, smoking behaviour, information on household smoking, symptoms, current treatment, doctor consultations, and results from diagnostic tests, when performed. Participants will also be asked to complete the standardized LCQ questionnaire on day 0. Participants will be instructed on how to complete the LCQ and that the GP can answer any questions they may have. Participants are also informed about the follow-up phone calls by the research staff/study nurse and that the next phone call appointment will be at day 7 of the trial. After completion of the LCQ the physician will enter all relevant patient information and contact data in the paper CRF and send the data to the CTU in order to facilitate access by the research staff/study nurse. Follow-up calls are carried by the CTU at the University Hospital Basel.

After completion of the LCQ the GP gives the trial medication to the patient.

#### **9.3.2 Day 7 (+2 days), Phone Call 1**

Patients will be called by study research staff/study nurses to complete the LCQ and to answer other questions regarding cough status, side effects, concomitant therapy, cessation of cough, re-consultations/hospitalisation, AE, SAE. If participants cannot be reached, the study nurse/research staff will send a reminder email and try calling back in the next 2 days from day 7.

#### **9.3.3 Day 14 (+2 days), Phone Call 2**

Patients will be called by study research staff/study nurses to complete the LCQ and to answer other questions regarding cough status, side effects, concomitant therapy, cessation of cough, re-consultations/hospitalisation, AE, SAE. If participants cannot be reached, the study nurse/research staff will send a reminder email and try calling back in the next 2 days.

#### **9.3.4 Day 28 (+2 days), Phone Call 3**

Patients will be called by study research staff/study nurses to complete the LCQ and to answer other questions regarding cough status, side effects, concomitant therapy, cessation of cough, re-consultations/hospitalisation, AE, SAE. If participants cannot be reached, the study nurse/research staff will send a reminder email and try calling back in the next 2 days.

### 9.3.5 Month 3 (+7 days), Phone Call 4

Patients will be called by the research staff/study nurses to complete the LCQ and to answer other questions regarding cough status, side effects, concomitant therapy, cessation of cough, re-consultations/hospitalisation, AE, SAE. If participants cannot be reached, the study nurse/research staff will send a reminder email and try calling back in the next 7 days.

## 10. SAFETY

### 10.1 Drug studies

During the entire duration of the study, adverse events (AEs) of special interest, as listed in the follow-up CRF, and all serious adverse events (SAEs) are collected, fully investigated and documented in source documents and case report forms (CRFs). Study duration encompasses the time from when the participant signs the informed consent (at randomization) until the last protocol-specific procedure at follow-up (month 3 from randomization) has been completed. However, we expect that the incidence of AEs or SAEs will be low, as the study uses an approved standard treatment for different conditions (asthma, COPD) which have a comparable pathogenesis to post-infectious cough. Please refer to section 10.1.2 for details on reporting.

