### **4.4 Safety Objectives**

To evaluate the impact of oral prednisone on:

- Safety outcomes, i.e. re-consultations at GP and/or hospitalisations
- Total AE within 3 months after randomization
- SAE within 3 months after randomization.

To assess any potential harms, we will evaluate any AE and specifically SAE according to the WHO-UMC causality categories “certain”, “probable”, “possible”, and “unlikely” (16).

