### 5.4 Safety Outcomes

- Incidence rate of re-consultations at GP and/or hospitalisations within 3 months following randomisation
- Total AE within 3 months after randomization
- SAE within 3 months after randomization
- Changes in glucose levels for patients with pre-study controlled diabetes that are deemed by GP to exceed the hypothesized benefit on cough.

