#### **9.2.4.2 Laboratory parameters**

Not applicable.

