#### 10.1.1 Definition and assessment of (serious) adverse events and other safety related events

An **Adverse Event (AE)** is any untoward medical occurrence in a patient or a clinical investigation participant administered a pharmaceutical product and which does not necessarily have a causal relationship with the study procedure. An AE can therefore be any unfavourable and unintended sign (including an abnormal laboratory finding), symptom, or disease temporally associated with the use of a medicinal (investigational) product, whether or not related to the medicinal (investigational) product.

A **Serious Adverse Event (SAE)** is classified as any untoward medical occurrence that:

- results in death,
- is life-threatening,
- requires in-patient hospitalization or prolongation of existing hospitalisation,
- results in persistent or significant disability/incapacity, or
- is a congenital anomaly/birth defect.

In addition, important medical events that may not be immediately life-threatening or result in death, or require hospitalisation, but may jeopardise the patient or may require intervention to prevent one of the other outcomes listed above should also usually be considered serious.

Examples of such events are intensive treatment in an emergency room or at home for allergic bronchospasm, blood dyscrasias or convulsions that do not result in hospitalisation, or development of drug dependency or drug abuse.

SAEs should be followed until resolution or stabilisation. Participants with ongoing SAEs at study termination (including safety visit) will be further followed up until recovery or until stabilisation of the disease after termination.

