#### Assessment of Causality

[name]. med. [name] (Sponsor-Investigator) and [name]. med. [name] will review all SAEs and make a causality assessment of the event to the study drug, based on the criteria listed in the ICH E2A guidelines:

| Relationship | Description                                                                               |
|--------------|-------------------------------------------------------------------------------------------|
| Definitely   | Temporal relationship
Improvement after de-challenge*
Recurrence after re-challenge |

|                                                                                          |                                                                                   |
|------------------------------------------------------------------------------------------|-----------------------------------------------------------------------------------|
|                                                                                          | (or other proof of drug cause)                                                    |
| Probably                                                                                 | Temporal relationship
Improvement after de-challenge
No other cause evident |
| Possibly                                                                                 | Temporal relationship
Other cause possible                                     |
| Unlikely                                                                                 | Any assessable reaction that does not fulfil the above conditions                 |
| Not related                                                                              | Causal relationship can be ruled out                                              |
| *Improvement after de-challenge only taken into consideration, if applicable to reaction |                                                                                   |

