#### 11.4.5 Safety analysis

Total number and percentages will be calculated for incidence rate of re-consultations at GP and/or hospitalizations within 3 months following randomization, and total AE and SAE stratified by WHO-UMC causality categories (16) within 3 months after randomization.

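### The safety outcomes, the rules for collecting them and the planned analysis contradict each other on AE scope, causality scale and glucose

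*Protocol*

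**What the plan says.** **AE scope.** Section 5.4 lists as a safety outcome "Total AE within 3 months after randomization". The synopsis and section 9.2.2 do the same, and section 4.4 says that "we will evaluate any AE and specifically SAE according to the WHO-UMC causality categories". The definition in section 10.1.1 is the usual broad one: "An AE can therefore be any unfavourable and unintended sign". Section 10.1 sets a narrower collection rule: "adverse events (AEs) of special interest, as listed in the follow-up CRF, and all serious adverse events (SAEs) are collected". Section 10.1.1 (under Assessment of Severity) and section 10.1.3 also speak of AEs of interest. Section 9.2.4.1 words the scope in a third way, as possible corticosteroid side effects and complications. Sections 9.2 and 9.3.2 to 9.3.5 have the callers ask about AEs without restriction.

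**Causality.** Section 11.4.5 reports "total AE and SAE stratified by WHO-UMC causality categories (16) within 3 months after randomization". Sections 4.4, 9.2 and 10.1.1 (under Assessment of Severity) name four WHO-UMC categories: certain, probable, possible and unlikely. Section 10.1.1 (under Assessment of Causality) has two reviewers look at all SAEs and "make a causality assessment of the event to the study drug, based on the criteria listed in the ICH E2A guidelines". The table there has five levels, the last being Not related.

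**Glucose.** Section 5.4 lists "Changes in glucose levels for patients with pre-study controlled diabetes" as a safety outcome, qualified by the GP's judgement of the change against the hoped-for benefit on cough. Section 9.2.4.2, on laboratory parameters, reads "Not applicable".

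**The concern.** Section 4.1 says that the trial is to describe a safety profile as well as efficacy, and section 3.7 treats safety as a serious matter even for short steroid courses. A safety table can be read only if its label matches what was recorded. If staff follow section 10.1, non-serious events off the CRF list are not collected, and no later analysis plan can recover them. A reader of the results would take total AE at face value.

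The causality mismatch means that one SAE can carry two ratings with no rule for choosing between them. The glucose item promises a metabolic safety result although the protocol plans no data for it, while section 3.7 itself names disordered glucose metabolism among the documented effects of short-term prednisone.

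Outcome definitions and event-collection rules belong in the protocol, so these conflicts cannot simply be left to the statistical analysis plan.

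**Working it through.** No arithmetic in the protocol is at issue. The check sets the sections side by side.

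**1. AE scope**

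| Role | Section | Scope of non-serious AEs |
|---|---|---|
| Objective | 4.4 | any AE |
| Outcome | Synopsis, 5.4, 9.2.2 | total AE |
| Definition | 10.1.1 | any untoward occurrence, related or not |
| Call content | 9.2, 9.3.2 to 9.3.5 | AE, unrestricted |
| Recording | 9.2.4.1 | possible corticosteroid side effects |
| Collection | 10.1 | special interest, listed in the follow-up CRF |
| Causality rating | 10.1.1, Assessment of Severity | AEs of interest |
| Follow-up | 10.1.3 | AEs of interest |
| Analysis | Synopsis, 11.4.5 | total AE |

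Let S be the number of SAEs, L the number of listed non-serious AEs and U the number of unlisted non-serious AEs. The outcome as named is S + L + U. The collection rule in section 10.1 yields S + L. The shortfall is U in each arm. U is zero only if the list, or an open field in the form, catches everything. The follow-up CRF is an appendix that is not shown, so U cannot be bounded further. Staff who work from sections 9.2 and 9.3 would record some of U and staff who work from section 10.1 would not. The count therefore depends on which section is followed.

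**2. Causality**

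| Five-level table (SAEs) | Four named WHO-UMC categories (AEs or AEs of interest, and SAEs) |
|---|---|
| Definitely | Certain |
| Probably | Probable |
| Possibly | Possible |
| Unlikely | Unlikely |
| Not related | no counterpart |

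The alignment of the first four rows is by name only, because the protocol states no mapping. Section 11.4.5 tabulates by WHO-UMC. Section 10.1.1 has the study team rate AEs of interest and SAEs on WHO-UMC, so that table can be filled. What is missing is a rule for which of the two SAE ratings is reported, and a place for an SAE judged Not related. The WHO-UMC causality rating also stands under a heading about severity, where a reader may miss it.

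**3. Glucose**

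| Where a glucose value or its analysis would have to appear | What the protocol has |
|---|---|
| Study schedule (also in section 9.1) | no glucose row |
| 1.4 and 9.2.4.2, laboratory | not applicable |
| 9.2.4.3, baseline diagnostics recorded if done | glucose not listed |
| 9.3.2 to 9.3.5, call content | no glucose item |
| 11.4.5, safety analysis | glucose not mentioned |
| 9.2.4.3, after inclusion | laboratory tests at the GP's discretion |

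Only the last row could supply values, and it neither requires a test nor says that the result is recorded for the trial. Section 5.4 gives no time point or threshold for the change.

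**The case against.** The strongest defence is that the protocol contains enough to produce most of the safety results. Four stronger readings are tempting, and the text does not support them.

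- A reader might infer that no AE total can exist in the data. That goes too far: the calls ask about AEs without restriction, and the unseen follow-up CRF may have an open field. What stands is a contradiction between sections, and an understated total if section 10.1 is the rule followed.
- A reader might infer that the causality table cannot be filled, or that nobody rates non-serious events on its scale. Section 10.1.1 gives exactly that task to the study team for AEs of interest and SAEs, and section 9.2 names the same scale. Nor need an SAE judged unrelated disappear, since the SAE total is an outcome in its own right. What stands is the pair of unreconciled scales.
- A reader might infer that the glucose outcome is bound to be empty. The GP may order laboratory tests after inclusion, and the outcome is framed as a GP judgement. What stands is that no measurement is planned. Its absence from section 11.4.5 could be made good in an analysis plan, but an analysis plan cannot supply the data.
- A reader might infer a bias between the arms. Collection is the same in both arms and blinded, and the protocol gives no reason to expect a difference in direction. What stands is that the level in both arms is understated.

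**Conclusion.** The point holds as an internal inconsistency in three parts.

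First, the AE outcome and its analysis are wider than the collection rule in section 10.1. If that rule is followed, the reported total is too low in both arms by the number of unlisted non-serious events. That number cannot be estimated from the documents, because the CRF list is not shown.

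Second, SAEs carry two causality ratings with no rule or mapping, and one of the five levels has no counterpart among the four named WHO-UMC categories. The planned table can still be produced.

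Third, the glucose outcome has no scheduled measurement, no recording item named in the protocol and no analysis stated there. Any values would come from discretionary testing.

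SAE counts, re-consultations and hospitalisations are not affected by the AE-scope conflict. The conclusion rests on the protocol text alone. An open AE item in the follow-up CRF would reduce the practical effect of the first part, but the sections would still need to be reconciled.

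**What to change.** 1. **AE scope.** Choose one of two options and carry it through.
   - Rename the outcome to AEs of special interest and SAEs in the synopsis and in sections 4.4, 5.4, 9.2.2 and 11.4.5, and align the call wording in sections 9.2 and 9.3. Section 5.2 lists no AE outcome and needs no change.
   - Or keep total AE, change sections 10.1, 10.1.1 and 10.1.3 so that all AEs are collected, and make sure that the follow-up CRF has an open item for any other event.
2. **Causality.** Use one scale that includes a not-related level for both rating and tabulation, and state that it covers the collected non-serious AEs as well as SAEs. Otherwise, state a mapping between the two scales and say which SAE rating is reported. Move the causality text out from under the severity heading.
3. **Glucose.** Delete the outcome from section 5.4, or redefine it as a glycaemic event reported by the GP or the patient in participants with diabetes, recorded at the existing calls and listed in section 11.4.5.

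The cost is protocol wording, at most one open AE item in the existing follow-up form and, if the glucose outcome is kept, one glycaemic item at the same calls. No visit, laboratory test or change in sample size is needed.

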#### 10.1.1 Definition and assessment of (serious) adverse events and other safety related events

An **Adverse Event (AE)** is any untoward medical occurrence in a patient or a clinical investigation participant administered a pharmaceutical product and which does not necessarily have a causal relationship with the study procedure. An AE can therefore be any unfavourable and unintended sign (including an abnormal laboratory finding), symptom, or disease temporally associated with the use of a medicinal (investigational) product, whether or not related to the medicinal (investigational) product.

A **Serious Adverse Event (SAE)** is classified as any untoward medical occurrence that:

- results in death,
- is life-threatening,
- requires in-patient hospitalization or prolongation of existing hospitalisation,
- results in persistent or significant disability/incapacity, or
- is a congenital anomaly/birth defect.

In addition, important medical events that may not be immediately life-threatening or result in death, or require hospitalisation, but may jeopardise the patient or may require intervention to prevent one of the other outcomes listed above should also usually be considered serious.

Examples of such events are intensive treatment in an emergency room or at home for allergic bronchospasm, blood dyscrasias or convulsions that do not result in hospitalisation, or development of drug dependency or drug abuse.

SAEs should be followed until resolution or stabilisation. Participants with ongoing SAEs at study termination (including safety visit) will be further followed up until recovery or until stabilisation of the disease after termination.

#### Assessment of Causality

[name]. med. [name] (Sponsor-Investigator) and [name]. med. [name] will review all SAEs and make a causality assessment of the event to the study drug, based on the criteria listed in the ICH E2A guidelines:

| Relationship | Description                                                                               |
|--------------|-------------------------------------------------------------------------------------------|
| Definitely   | Temporal relationship
Improvement after de-challenge*
Recurrence after re-challenge |

|                                                                                          |                                                                                   |
|------------------------------------------------------------------------------------------|-----------------------------------------------------------------------------------|
|                                                                                          | (or other proof of drug cause)                                                    |
| Probably                                                                                 | Temporal relationship
Improvement after de-challenge
No other cause evident |
| Possibly                                                                                 | Temporal relationship
Other cause possible                                     |
| Unlikely                                                                                 | Any assessable reaction that does not fulfil the above conditions                 |
| Not related                                                                              | Causal relationship can be ruled out                                              |
| *Improvement after de-challenge only taken into consideration, if applicable to reaction |                                                                                   |

### Unexpected Adverse Drug Reaction

An “unexpected” adverse drug reaction is an adverse reaction, the nature or severity of which is not consistent with the applicable product information (e.g. Investigator’s Brochure for drugs that are not yet approved and Product Information for approved drugs, respectively).

### Suspected Unexpected Serious Adverse Reactions (SUSARs)

[name]. med. [name] (Sponsor-Investigator) and [name]. med. [name] evaluate any SAE that has been reported regarding seriousness, causality and expectedness. If the event is related to the investigational product and is both serious and unexpected, it is classified as a SUSAR.

Note: In case of double-blinded studies, unblinding is needed in order to determine a SUSAR. Treatment allocation should not be disclosed to the investigator, nor to the study staff, in order not to make the subject ineligible.

### Assessment of Severity

To assess any potential harms, the study team evaluates AE of interest and specifically SAE according to the WHO-UMC causality categories “certain”, “probable”, “possible”, and “unlikely” (16).

The severity grading scale used for the study are described in the „Common Terminology Criteria for Adverse Events“, CTCAE Version 5.0 ([https://ctep.cancer.gov/protocolDevelopment/electronic\\_applications/ctc.htm#ctc\\_50](https://ctep.cancer.gov/protocolDevelopment/electronic_applications/ctc.htm#ctc_50)) terminology is going to be used for adverse events occurring throughout this study: Grade 1 - Mild, Grade 2 - Moderate, Grade 3 - Severe, Grade 4 - Life-threatening, Grade 5 - Death.

## 10.1.2 Reporting of serious adverse events (SAE) and other safety related events

### Reporting of SAEs

All participant SAEs captured during the follow-up interviews will be recorded by study nurses/staff who will report them within a maximum of 24 hours via the eCRF secuTrial® to [name]. med. [name], the Sponsor-Investigator for the study.

Participant SAEs that are reported to GPs or self-reported by participants by directly contacting the OSPIC study team in Liestal will be recorded and reported within a maximum of 24 hours via email or post to [name]. med. [name], the Sponsor-Investigator for the study.

[name]. med. [name] will sign off, evaluate the SAE for causality and, if necessary, report them to the EKNZ.

SAEs resulting in death are reported to the ENKZ (via [name]. med. [name]) via BASEC within 7 days.

